## Abstract

**Introduction::**

Cardiovascular diseases are the world's most common causes of morbidity and mortality in the population, including Central Europe. Cardiac rehabilitation (CR) is an effective preventive approach that includes several core components. Physical training is identified as an integral and essential part of CR. Training can positively influence several cardiovascular risk factors in people diagnosed with coronary heart disease and prevent them from clinical events. Our study aims to research the method of high-intensity interval training (HIIT) in a home environment using telerehabilitation. We assume that the HIIT form of telerehabilitation, using a heart rate monitor as a tool for backing up training data, can improve cardiorespiratory fitness and lead to higher peak oxygen uptake than the traditional moderate-intensity continuous training (MICT).

**Methods::**

This study is designed as a monocentral randomized controlled trial at University Hospital Brno in the Czech Republic. After the coronary heart event, the suitable patients will be randomized (1:1 ratio) and separated into 2 groups: the experimental HIIT group and the control MICT group. Both groups undergo a 12-week telerehabilitation with a 1-year follow-up period. Study participants will be telemonitored during physical training in their home environment via a heart rate monitor and a web platform. Once a week, the patients will give their feedback and motivation by a telephone call.

The primary outcome observed will be the effect of intervention expressed by changes in cardiorespiratory fitness. Secondary outcomes will be the health-related quality of life, anxiety, training adherence, body composition, safety, and satisfaction.

**Discussion::**

The HIIT is widely researched predominantly in a center-based supervised form. Our study differs from others by the use of telemedicine and smart technologies in home-based settings. Previous home-based cardiac telerehabilitation studies have focused primarily on MICT, which has demonstrated feasibility, and results have shown similar improvements as center-based CR. There is a presumption that HIIT may be superior to MICT. However, it can be complicated to self-dose the method in the home environment. Investigators expect that HIIT research will provide insight into the possibilities of telemedicine feasibility, effect, and limitations of coronary heart disease patients’ use at low to moderate cardiovascular risk.

## Introduction

1

Coronary heart diseases (CHD) represent a significant part of all deaths caused by cardiovascular diseases worldwide.^[1]^ CHD mortality prevalence is supposed to increase by 2030 (≈17%).^[2]^ Therefore, it is essential to work on secondary preventative strategies that reduce cardiovascular disease impact. Cardiac rehabilitation (CR) is a complex secondary – preventive intervention that makes an effort to reduce cardiovascular disease risks and to promote, accept, and keep a healthy lifestyle.^[3]^ Secondary prevention recommendations emphasize the importance of receiving a many-sided approach to manage cardiovascular risks.^[4]^ The physical activity represents the essential CR component and plays a vital role in secondary cardiovascular prevention. Systematic exploration of the Cochrane database recorded approximately 12% mortality reduction from all causes and almost 26% of cardiovascular mortality after comprehensive CR program, including physical training.^[5]^ Other meta-analyses support these findings.^[6,7]^ Despite all the recognized benefits, global providing of outpatient CR programs is insufficient.^[8]^ The application of these programs in the Czech Republic is comparable with other world parts. Implementing and completing outpatient programs remains low (≈10%).^[9]^

Considering the main reasons for absence in such programs, patients usually mention technical complications, such as commuting difficulties, time demandingness, or fixed program schedule.^[10]^ Currently, CR focuses on possibilities that might increase patients’ attendance according to their preferences and needs. One of such approaches that shall be explored is using telerehabilitation.

Telerehabilitation involves using information and communication technologies for providing remote health care services.^[11]^ In terms of using CR, telerehabilitation uses information and communication technologies, providing feedback and consultancy from specialists in hospital centers. Telerehabilitation has great potential in improving overall CR uptake.^[12]^

A systematic review of earlier telemedicine CR studies revealed a significant influence of cardiovascular risk factors, including low adherence to the training programs, higher cholesterol, and systolic blood pressure. At the same time, physical fitness values were higher in patients who enrolled in telemedicine groups. Some proofs indicate that telerehabilitation may improve health-related quality of life and decrease CR program costs.^[13]^ Physiological monitoring has been recently identified as an incredibly important trend for future development; nevertheless, its implementation has not yet been adequately managed.^[14]^ Current telemonitoring possibilities are sufficient and enable the analysis of the performed physical training and heart rate (HR). Telecommunication might replace traditional communication tools and implement fast-developing technologies enabling faster and individualized possibilities.^[15]^

A recently completed study demonstrated an intervention using the HR monitor and internet as an effective and sufficient way of providing telerehabilitation in patients after CHD.^[16]^ A 12-week home-based program showed that telerehabilitation leads to similar results in cardiopulmonary fitness as outpatient training. Although this study proved the feasibility and efficiency of telerehabilitation, further randomized control studies are needed in this field.

In the presented research study, we want to verify the inclusion of high-intensity interval training (HIIT) in home-based settings using telerehabilitation. We hypothesize that the HIIT telerehabilitation via HR monitor will improve cardiorespiratory fitness and lead to higher peak oxygen consumption than traditional medium-intensity continuous training (MICT).

## Methods

2

### Study design

2.1

This study is designed as a monocentral randomized controlled trial at University Hospital (UH) Brno in the Czech Republic. All participants provided written informed consent before entering the study. Study data will be collected at baseline (T0), after 3 months (T1), and after 12 months (T2). (Fig. 1) The Institutional Ethics committee approved the study protocol of the UH Brno, Czech Republic. The trial is registered as recommended by the World Health Organization at ClinicalTrials.gov with number NCT04552652. Study data will be password-protected, and only the designated investigator of the research team can access it. The participants’ data will be processed and backed up following the current European General Data Protection Regulations.

**Figure 1 F1:**
[figure not shown]
Flowchart of the study protocol.

### Population and randomization

2.2

Participants suitable for this study will be the patients of UH Brno older than 18 years, diagnosed with CHD (angina pectoris or myocardial infraction in last eight weeks), with low or medium cardiovascular risk status (without residual coronary stenosis, value of left ventricular ejection fraction more than 40%).^[17]^ After heart revascularization, the participants will be referred to the II. phase of CR with the recommended pharmacotherapy. Further eligibility criteria will be clinically stable state, ability to perform physical training and cardiopulmonary exercise test (CPET), ability to understand and write in the Czech language, internet connection at home, and literacy with information and communication technology. The participants’ recruitment and allocation will be monitored by the study cardiologist, physiotherapist, or an assistant in UH Brno, Czech Republic.

The exclusion study criteria are patients hospitalized with CHD in the previous 6 weeks, severe psychological or cognitive disorders, serious training limitations besides CHD, participation in another training program under supervision, and contraindications for CPET.

Participants will be randomized (in 1:1 ratio) into the experimental HIIT group and control the MICT group via computer sequence generated by the study statistician. The treatment allocation will be hidden until the completion of the baseline of the initial examinations in sequentially numbered, sealed, opaque envelopes. The study participants cannot be blinded by treatment allocation, but researchers who perform line examinations will be blinded by treatment allocation.

### Training program

2.3

The exercise program is prescribed according to the current recommendations of the European Society of Cardiology (ESC).^[18]^ In both groups, the patients participate in a 12-week telerehabilitation training program with three training sessions a week. All participants will perform home-based physical training with prescribed exercise intensity according to HR max, determined by the CPET assessment.

The prescription of exercise intensity is shown in Figure 2. The HIIT group warms-up for 5 minutes at moderate intensity (65%–75% of HRmax). After warm-up exercise, core training will continue in 4 minutes intervals at high-intensity to reach the target HR zone (85%–95% of HRmax). Each interval will be separated by 3 minutes of active recoveries (at 65%–75% of HRmax). The session ends with a 3-minute cool-down phase. Overall training exercise time will be 33 minutes; isocaloric compared to the MICT group. Patients in the MICT group will perform a 41-minute constant workout with intensity at 65% to 75% of HRmax, representing the same total training load as the HIIT group. All participants will train using an HR monitor during each training session in the home environment.

**Figure 2 F2:**
[figure not shown]
Home-based telerehabilitation scheme. The figure represents home-based physical training via telemonitoring and remote guidance. Icons illustrate cardiac telerehabilitation form. The differences in training prescription between the two study groups are shown in the diagram at the top left.

One to 3 pilot training sessions in the outpatient CR center under the supervision of a physiotherapist will undertake all participants before the telerehabilitation program. These pilot sessions’ objective is to educate and practice how to use a wearable HR sensor (Polar H10). As a part of the education, the patients learn how to adhere to the prescribed duration of the physical training and intensity by checking the correct HR zone. Further on, the patients will be instructed about preferred training modality in a home-based environment (cycling, walking, or Nordic walking) and receive advice on how to perform the modality. Subsequently, the patients will be educated on how to use the HR sensor correctly and upload the training data to the web application (Polar Flow).

Throughout the study, the patients will be able to check training data and results to see if they are meeting their training goals. The personal coach (physiotherapist) will be able to view the data in the application and also provide remote guidance (motivation, feedback on the frequency, duration, and intensity of training) via a preferred phone call once a week (Fig. 2). After 3 months, the telemonitored training sessions will be completed. Patients will be recommended to keep on doing exercises with the HR sensor and web application. A long-term effect will be assessed in a 1-year follow-up.

### Telemonitoring

2.4

The personal coach will keep telemonitoring participants – checking their physical intervention and provide them with feedback and support. At the beginning of the training program, the personal coach will meet each patient separately and set personal training goals.

Such an approach can positively influence the overall improvement because it concretizes relations and enables 1 to individualize each patient's possibilities.

The activity and cooperation will be supported to make the patient feel responsible for their results. Remote telemonitoring and supervision will meet the following criteria: The training program will be set into three parts. The golden standard for CR recommends the warm-up phase, core exercise, and cooling-down phase. Each phase will take the exact time and be set training intensity according to HRmax assessed in CPET. The coach will monitor whether the patient keeps the stages and the training HR intensity. Based on the analysis, the coach will make some changes or provide recommendations for the program's rest.

### Outcomes

2.5

The primary study outcome is the cardiorespiratory fitness value, assessed at the beginning of the intervention and after a 12-week and 1-year follow-up period. The study's secondary intervention outcome is the health-related quality of life, anxiety and depression, body composition, the incidence of treatment-emergent adverse events assessed by 5-grade scale, training adherence (number of compliant participants, average exercise time, overall completition rate). Assessment of the cardiorespiratory fitness, health-related quality of life, depression, anxiety, and body composition will be evaluated at the beginning of the study (T0), after 12-weeks (T1), and after 1-year period (T2).

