### Training adherence and adverse events

2.8

Training adherence and incidence of the adverse events will be recorded in the exercise datasheets from the telemonitoring platform for both groups during the 12-weeks training program.

According to the number of completed training sessions, training adherence will be evaluated through the Polar Flow web application as the overall completion rate of prescribed exercise lessons (100% = 36). The training diary in the web application will provide information about the total average time of all exercises in the defined HR zone and the total number of compliant participants (the criterion of compliance with the rehabilitation program is set at 70% of the prescribed training sections). According to the data obtained, investigators will assess the total training program completion.

The study participants will be encouraged to use the contact details for reporting the incidence of treatment-emergent adverse events at any time throughout the study period. The scale will assess the type, incidence, and severity of adverse events (grade 1: mild, asymptomatic or mild symptoms; grade 2: moderate, minimal; grade 3: severe or medically significant; grade 4: life-threatening consequences; and grade 5: death) will be noted.

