### Statistics

2.11

The Shapiro-Wilk test will be used to evaluate normality. Comparisons between subjects will be made using the Student *t* test and Mann–Whitney *U* test. The 2-tailed Fisher exact test will test differences in proportions. Data will be summarized as a mean ± standard deviation; *P* values < .05 will be considered statistically significant. Statistica software 12.0 (TIBCO Software Inc, Palo Alto) will be used for statistical analysis.

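### Average exercise time counts as adherence but is not scaled to prescriptions that differ by arm (33 vs 41 minutes), so equally adherent arms differ by 8 minutes per session.

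*Protocol article*

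**What the plan says.** Section 2.5 (Outcomes) of the protocol article lists three components of one secondary outcome: "training adherence (number of compliant participants, average exercise time, overall completition rate". Section 2.8 says that the diary in the web application will supply "information about the total average time of all exercises in the defined HR zone". No denominator is attached to this time.

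The other two components do have one. The completion rate is counted against 36 prescribed sessions, and a participant is compliant at 70% of the prescribed sessions. Both arms have 36 sessions, so these denominators are common to the arms.

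The prescribed time is not common to the arms. For HIIT, section 2.3 (Training program) states: "Overall training exercise time will be 33 minutes; isocaloric compared to the MICT group". For the control arm it states: "Patients in the MICT group will perform a 41-minute constant workout with intensity at 65% to 75% of HRmax".

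Section 2.11 (Statistics) gives one general rule for group comparisons, "Comparisons between subjects will be made using the Student" t test and the Mann–Whitney U test, with P < .05 as the threshold. It does not list the outcomes to which the rule applies.

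**The concern.** An adherence measure should take the same value in two arms that follow their prescriptions equally well. Time in minutes cannot do so here, because the design matches the arms on training load and therefore gives them different session lengths. A lower mean time in the HIIT arm would be expected even if every patient did exactly what was asked, and a reader who sees it under the adherence heading would take it as poorer adherence.

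This matters because the article presents the trial partly as a test of whether HIIT can be carried out at home. The abstract's discussion says that self-dosing HIIT at home may be complicated, and section 3 (Discussion) repeats the doubt and stresses reliable assessment of compliance. A built-in HIIT deficit would seem to confirm that doubt whether or not it is true.

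**Working it through.** **Inputs**
- HIIT session: 33 minutes (2.3).
- MICT session: 41 minutes (2.3), taken as the whole session because it is matched to the HIIT total.
- Sessions prescribed: 36 in each arm (2.8).
- Participants: 38 per arm (2.12).
- Significance level: .05 (2.11), taken as two-sided for the t test.
- SD of exercise time: not given, so a range is assumed.

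**The plan's own figures**
- HIIT session: 5 min warm-up + 4 × 4 min intervals + 3 × 3 min recoveries + 3 min cool-down = 5 + 16 + 9 + 3 = 33. The text does not state the number of intervals; four is the number that gives 33 (three gives 26, five gives 40).
- Sample size: with a difference of 2.8 and an SD of 4.3, a two-sided 5% test at 80% power needs 38 per arm, 76 in total, as stated in 2.12.

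**Gap under full adherence in both arms**
- Per session: 41 − 33 = 8 minutes; 33/41 = 0.805, so HIIT is 19.5% lower.
- Over the programme: 36 × 33 = 1,188 and 36 × 41 = 1,476, a difference of 288 minutes.

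**Sign reversal**
- HIIT at 95% of prescription: 0.95 × 33 = 31.35 minutes.
- MICT at 85% of prescription: 0.85 × 41 = 34.85 minutes.
- The more adherent arm has the lower mean. In minutes, fully adherent HIIT only equals MICT at 33/41 = 80.5% of its prescription.

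**Chance of P < .05 from the 8-minute gap alone**

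Two-sample t test, noncentrality = 8 / (SD × √(2/n)). For n = 38 and SD 8 this is 8 / (8 × 0.2294) = 4.36.

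| Assumed SD (min) | 38 per arm | 30 per arm |
|---|---|---|
| 8 | 99% | 97% |
| 10 | 93% | 86% |
| 12 | 82% | 72% |
| 15 | 63% | 53% |
| 20 | 41% | 33% |

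The 30-per-arm column illustrates losses; the article gives no drop-out rate. The chance is at least 80% up to an SD of about 12.3 minutes with 38 per arm, or 10.9 with 30. If patients stay close to their prescription, the SD lies towards the low end.

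**After scaling to prescription**
- Full adherence: 33/33 = 41/41 = 100%, so the built-in difference is zero and the false-positive rate returns to the nominal 5%.
- The 95% and 85% arms keep their true order.

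**The case against.** The strongest reply is that the article commits to neither raw minutes nor a test on them. It gives no unit or formula for exercise time, section 2.8 uses the language of reporting, and section 2.11 assigns no test to particular outcomes. A condensed article may leave such a derivation to the full protocol or analysis plan. Two of the three adherence components are already relative to prescription, and exercise time could be read beside them as delivered dose.

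Part of this stands. Minutes and a between-arm test are the natural reading, not an explicit statement. But the article does more than omit a detail. It names time as adherence, gives denominators to the other two components, gives none to the one component whose prescribed value differs by arm, and sets a general between-group test. Followed as written, that yields a misleading contrast.

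Two stronger readings are tempting, and the document supports neither.

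- A reader might infer that fully adherent HIIT patients are bound to test as significantly less adherent. That needs an SD which the article does not give; at SD 20 the chance is 41%. The bias is present at any SD, but significance is not assured.
- A reader might infer a gap of 16 vs 41 minutes (25 minutes, 61% lower), since 2.3 says "core training will continue in 4 minutes intervals at high-intensity to reach the target HR zone (85%–95% of HRmax" and 2.8 counts "total average time of all exercises in the defined HR zone". But 2.3 also sets 65%–75% of HRmax for the HIIT warm-up and recoveries, so the defined zone may equally mean the zone set for each phase. The 16-minute case rests on one reading of an ambiguous phrase.

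**Conclusion.** The concern holds in a limited form. On the plain reading, average exercise time reflects what each arm was prescribed rather than how well it was followed: an 8-minute (19.5%) HIIT deficit under equal, full adherence, with possible reversal of sign when HIIT adherence is better. The size of this gap follows from the article's own figures and, apart from taking 41 minutes as the whole MICT session, needs no outside assumption.

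The chance that it produces a significant result does rest on assumptions: a between-arm t test on minutes, 38 analysed per arm, and an SD that has to be supposed. Over SDs of 8 to 20 minutes it runs from about 99% to 41%.

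One of three components of one secondary outcome is affected. The completion rate, the 70% compliance criterion, the primary outcome and the sample size are not. The point should be corrected before analysis, but it does not threaten the trial's main conclusion.

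**What to change.** In 2.5 and 2.8:

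- Define exercise time for adherence as total minutes performed, as a percentage of the total minutes prescribed for the patient's arm (33 or 41 per session). Make any between-arm adherence comparison on that percentage.
- Report raw minutes, and minutes in each heart-rate zone, by arm as delivered dose: descriptively, without an adherence test.
- State which HIIT phases count towards the defined heart-rate zone.

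Dividing in-zone HIIT time by 16 minutes would not be a safe substitute. Heart rate has to climb into the zone in each of four intervals, so a patient who follows the prescription would still score below 100%. Section 2.3 also gives no zone for the HIIT cool-down, so a denominator for the remaining phases would be incomplete. Total minutes avoid both problems.

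The cost is a sentence or two and one variable derived from data already uploaded to the web application. No new data are needed and no prescription changes. The small downside is that raw minutes are no longer a tested outcome.

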### Cardiorespiratory fitness

2.6

Analysis and assessment of cardiorespiratory fitness will be processed via automated metabolic system Metalyzer 3b (Biophysics GmbH, Leipzig, Germany) and by the progressive increment CPET on bicycle ergometer Ergoselect 100 (Ergoline, Bitz, Germany) up to the level of limited symptom maximum. CPET will be set according to recommendations of ESC and the American Heart Association.^[19,20]^

The study will use ramp protocol for a stress test, including 2 minutes warming up at 10 watts, followed by 15 watts growths every minute for men and 10 watts growths for women with the final 2 minutes of cooling down at 10 watts.

Considering the maximum oxygen consumption is very difficult to reach in CHD patients, it is common to use peak assessed during the stress test as the average in the last 30 seconds of stress.^[20]^ The cardiologist will be present while testing the participants, estimates the abnormal signs on ECG, and independently values ventilation thresholds.

